## Introduction

1

Schizophrenia, schizoaffective disorder, and bipolar disorder are severe and enduring psychiatric conditions characterized by a lifelong pattern of emotional, behavioral, and cognitive symptoms (1–4). These conditions, albeit diagnostically distinct, share several clinical and epidemiological traits, including significant metabolic co-morbidity resulting in a reduction in life expectancy, ranging from 13 to 15 years (5) and up to 25 years in low-income countries (6, 7). Those suffering from chronic psychotic disorders endure the additional burden of poor metabolic health (8). Unfortunately, the currently available antipsychotic medications are only partially effective in assisting with symptom management and come with serious side effects, including diabetes, weight gain, and high blood pressure, leading to a greater prevalence of metabolic syndrome and cardiovascular disorders (9).

A major roadblock to developing better therapeutical approaches in serious mental illnesses, such as schizophrenia and bipolar disorder, is the lack of sufficient development in our understanding of disease mechanisms and the identification of potential new therapeutic targets. Since the serendipitous discovery of antipsychotics and lithium in the treatment of schizophrenia and bipolar disorder, respectively, the dominant mechanistic explanations have focussed mainly on major neurotransmitter systems, such as the dopaminergic, serotonergic, and glutamatergic neurotransmission (2, 4, 10). Targeting these systems by pharmaceutical agents has produced major improvements in managing key symptoms and the patient’s quality of life. However, they have also contributed to the development of clinically significant side effects, including motor, metabolic, and endocrine disturbances, which strongly and negatively influence quality of life and life expectancy (11). Those shortcomings of traditional pharmacological approaches have in turn driven recent efforts to identify underlying disease mechanisms as putative targets for symptom improvement and better quality of life for individuals with schizophrenia and bipolar disorder. The development of human genetics and the different-omics technologies, including genomics, transcriptomics, and metabolomics, have revealed the potentially interlinked role of inflammatory/immune mechanisms and altered systemic and brain bioenergetics in the pathophysiology of these disorders (12–16) (Figure 1). Here we briefly review the basics of brain bioenergetics and its alterations in schizophrenia and bipolar disorders to provide a strong mechanistic rationale for our clinical trial.

Although constituting just 2–3% of the total body weight, the adult human brain is responsible for the consumption of a disproportionately large fraction, nearly 20%, of the human body’s basal metabolic rate (17). Glucose is the main energy substrate in the brain (18). The high-energy molecule adenosine triphosphate (ATP) is produced from glucose through glycolysis, the non-oxidative breakdown of glucose to pyruvate and lactate in the cytoplasm, through the tricarboxylic acid (TCA) cycle and oxidative phosphorylation (OXPHOS) in the mitochondria (18). Reversing ion movements that generate neuronal post- and pre-synaptic responses consume most of the energy from ATP (19). Glucose is not only the major source of ATP but is also used for the biosynthesis of ribose to form ribonucleic acids, fatty acids, and cholesterol (Figure 2). In addition, glucose through the pentose-phosphate pathway (PPP) is involved in the protection against oxidative stress and through the TCA cycle in the production of amino acids such as glutamate and subsequently GABA (18). Neurons and glia cells cooperate in their energy production. Astrocytes take up glucose from the brain capillaries and metabolize it to lactate through glycolysis, which is transported to neurons through monocarboxylate transporters, a process called the astrocyte-neuron lactate shuttle (19). Neurons then convert lactate to pyruvate and generate ATP thought the TCA cycle and the OXPHOS (18). However, neurons are able to generate ATP directly through glycolysis, even in the presence of sufficient oxygen concentration (aerobic glycolysis), during heightened activity (18). Therefore, deficits in glucose and energy supply in neurons or in glia cells can impair the dynamic regulation of key brain circuits, ultimately resulting in abnormal brain function and behavior (20).

**Figure 1 fig1:**
[figure not shown]
Following Enrolment at T1, participants progress to an “adaptation period” of 2 weeks followed by 6 weeks of allocated dietary intervention until they reach the Mid-Point Visit [T2]. Participants will continue through for further 6 weeks to the Completion Assessment [T3] at week 14.

**Figure 2 fig2:**
[figure not shown]
Participants will be stratified to one of 8 groups, depending on their primary diagnosis, biological sex, and duration of illness greater or less than 5 years.

Systemic glucose metabolism abnormalities marked by hyperglycemia and insulin resistance have long been noted in schizophrenia, predating the advent of antipsychotic agents and in treatment-naïve, first-episode psychosis patients (21) In the brain, impairments in glucose metabolism and mitochondrial functions have been detected through diverse methodologies. Essentially, reduced expression of genes encoding various glycolytic enzymes, including the rate-limiting hexokinase, have been observed, alongside diminished levels of enzyme proteins and their activity (22), specifically in glutamatergic neurons in the dorsolateral prefrontal cortex in people with schizophrenia (23, 24). Furthermore, multiple mitochondrial impairments, including altered expression of electron transport chain enzymes, such as Complex-I and Complex-V (ATP-synthase), have been demonstrated in the brains of people with schizophrenia (25–27). Brain imaging studies have identified decreased glucose utilization in the frontal cortex (hypofrontality) and a switch to more glycolytic ATP production associated with elevated brain lactate levels (28, 29). These findings contribute to the conceptualization of schizophrenia as a disease of impaired brain bioenergetics (14).

Similarly, metabolomics and magnetic resonance spectroscopy indicate that energy dysregulation is a central feature of bipolar disorder pathophysiology (30–32). Accordingly, mania represents a condition of heightened cerebral energy metabolism facilitated by hyperglycolysis and glutaminolysis. When oxidative glucose metabolism becomes impaired in the brain, neurons can utilize glutamate as an alternative substrate to generate energy through oxidative phosphorylation. It has been hypothesized that the upregulation of glycolysis and glutaminolysis in this manner causes the brain to enter a state of heightened metabolism and excitatory activity which may underlie the subjective experience of mania (30). Supporting this hypothesis, recent studies have identified mitochondrial abnormalities and resulting elevation of deleterious free oxygen radicals in bipolar disorder (33–35). Taken together, recent progress in the neurobiological understanding of schizophrenia and bipolar disorder points toward the mechanistically important role of abnormal brain bioenergetics in their pathophysiology.

Ketogenic metabolic therapy, achieved via the consumption of a low carbohydrate (CHO)-high fat-containing diet (ketogenic diet; KD), elevates circulating ketone bodies, such as acetoacetate and beta-hydroxybutyrate. Ketone bodies can serve as an alternative energy source for impaired glucose metabolism and support mitochondrial function (36), thus potentially counteracting the underlying bioenergetic abnormalities in schizophrenia and bipolar disorder (37, 38). Three weeks of KD or beta-hydroxybutyrate administration effectively normalized behavioral impairments in a hypo-glutamatergic animal model of schizophrenia (39–41). After highly encouraging results from case studies showing dramatic improvements in a wide range of symptoms and quality of life in patients with schizophrenia on KD (42–45), a recent single-arm clinical trial in which patients with schizophrenia and bipolar disorder consumed a medically supervised KD, showed improvements in several psychiatric symptoms and metabolic functions (46). KD was also successfully used in a recent single-arm trial in patients with bipolar disorder (47). To indicate an increasing interest in ketogenic therapeutic interventions in psychiatry a recent pilot trial protocol aims to investigate the effect of a ‘ketogenic-mimicking diet’ (combining supplementation of ketone esters with a low glycemic index dietary intervention) on neural network stability, mood, and biomarker outcomes in the setting of bipolar disorder (48).

Taken together, positive results from extant preclinical studies, case studies, and uncontrolled clinical trials point toward a clinically significant role for ketogenic metabolic therapy in the treatment of serious mental illness and offer hope to millions of individuals worldwide, who suffer from those conditions. However, no data from randomized controlled clinical trials exist to date. Such clinical trial ought to compare the effects of KD with another dietary intervention under circumstances that are identical for all randomly assigned trial participants in every possible aspect, such as trial management, clinician’s attention, and outcome measures, to establish the specific contribution of the ketotic metabolic state on the outcomes of interest. Here we report the detailed protocol of a randomized controlled clinical trial to investigate the efficacy of ketogenic metabolic therapy on psychiatric, cognitive, and functional symptom improvement and metabolic changes in schizophrenia and bipolar disorder.

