**Design:**

A randomized placebo-controlled clinical trial of 100 non-hospitalized adult participants with a diagnosis of bipolar disorder, schizoaffective disorder, or schizophrenia who are capable of consenting and willing to change their diets.

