### Study design

2.1

This randomized placebo-controlled parallel-designed clinical trial is registered with the Australian New Zealand Clinical Trials Registry (ANZCTR), the mandated online register of clinical trials being undertaken in Australia, New Zealand, and other Oceanic Nations (Reg. No: ACTRN12623000854639).

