#### Allocation

2.1.3

Participants will be blinded to the study hypothesis and interact with clinicians who are kept blind to their group allocation as far as possible. Allocation will occur only after the initial psychiatrist assessment. If a psychiatrist becomes accidentally unblinded to a participant’s allocation during the running of the trial, a different team psychiatrist will be asked to continue the remaining time points assessment(s) for that participant. Participants in both groups will be treated identically in all respects except for the intervention being tested.

The study is being conducted at a single site at the Translational Research Facility, Australian Institute of Tropical Health and Medicine, James Cook University at Townsville Campus, Queensland, Australia. Human Research Ethics Approval (HREC/2022/QTHS/85408) for this study was received by the Townsville University Hospital HREC board, responsible for the study population’s catchment area.

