### Experimental intervention

2.2

The intervention involves a 12-week dietitian-led, medically supervised KD, designed to induce a state of nutritional ketosis. Several dietary regimes for achieving ketosis in adults exist including the Modified Atkins Diet (MAD)/ Modified Ketogenic Diet (MKD), Low Glycaemic Index Treatment (LGIT), and the Classical Ketogenic Diet (Table 2). These diets share a common principle of reducing carbohydrate (CHO) intake while increasing fat consumption. The variation in the degree of CHO reduction and fat increase distinguishes these regimes. In this trial, a MKD (2:1 ratio) will be implemented to induce ketosis in participants. The MKD was selected for its higher compliance rates (49, 50) and its allowance for greater flexibility and food variety compared to the classical ketogenic diet (4:1 ratio). The prescribed amount of macronutrient distribution will aim for approximately 75% of EER from fat, 5% from CHO, and the remaining from protein. Additionally, participants following the MKD will be recommended to supplement with a CHO-free multivitamin in accordance with best practice guidelines (49).

**Table 2 tab2:** Most commonly used therapeutic Ketogenic diets.

	Modified Atkins diet	Modified Ketogenic diet	Low glycaemic index treatment	Classic Ketogenic diet
Fat (%)	65	75	60	90
Carbohydrates (%)	10	5	10	4
Protein (%)	25	20	30	6

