### Control diet

2.3

The study’s control group adheres to a 12-week regimen of dietitian-led and medically supervised nutrition, aligning with the principles outlined in the Australian Guide to Healthy Eating (AGHE). Macronutrient intake, including carbohydrates, fat, and protein, is calculated to match individual factors such as age, weight, and level of physical activity as set out in the guidelines. Within this framework, the recommended optimal macronutrient ranges from the AGHE are encouraged, with protein comprising 11%, fats ranging from 20 to 35%, and the remainder from carbohydrates (see Table 3) (51).

**Table 3 tab3:** Ketogenic diet vs. the Australian guide to healthy eating.

Ketogenic diet	Australian guide to healthy eating
< 50 g of carbohydrates per day Total daily calories: 70–80% fat 5–10% carbohydrates 10–20% protein	Plenty of vegetables of different types and colors, and legumes/beans Fruit Grain (cereal) foods, mostly wholegrain and/or high cereal fiber varieties, such as breads, cereals, rice, pasta, noodles, polenta, couscous, oats, quinoa, and barley Lean meats and poultry, fish, eggs, tofu, nuts and seeds, and legumes/beans Milk, yogurt, cheese, and/or their alternatives, mostly reduced fat

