## Discussion

9

The rationale for this randomized controlled clinical trial is based on a converging line of evidence coming from recent studies showing a variety of brain bioenergetic abnormalities in schizophrenia and bipolar disorders, prior preclinical research demonstrating the efficacy of the ketogenic diet in animal models of schizophrenia, as well as recent encouraging results from case studies and pilot, single-arm clinical trials that indicate clear symptom improvement and better metabolic control in patients with serious mental illness on a ketogenic diet. We expect that the dietary metabolic interventions in our trial will result in beneficial changes in symptoms, everyday functioning, and overall metabolic health for our participants. The control diet, based on the AGHE guidelines, is likely superior in terms of its health effects compared to the participants’ usual dietary patterns because of its focus on incorporating whole grains, dietary fiber, plant-based proteins, and unprocessed food. We expect that the ketogenic metabolic therapy, with its targeted effect on brain and systemic energy metabolism, will result in further improvements in metabolic health, controlling psychiatric symptoms and improving overall functioning, above and beyond the control diet. In addition to establishing efficacy, our design will allow the assessment of the participant’s compliance with and adherence to a relatively restrictive dietary schedule that requires major deviations from their usual diet. This will be important for future dietary metabolic interventions in serious mental illness, where patients are generally perceived to be struggling with such challenges.

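### The trial is labelled placebo-controlled but compares two active diet packages, so neither a comparison with placebo nor an effect of ketosis alone can be concluded from it

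*Protocol article*

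**What the plan says.** **Label.** The Abstract (Design) describes "A randomized placebo-controlled clinical trial of 100 non-hospitalized adult participants". Section 2.1 repeats the label: "This randomized placebo-controlled parallel-designed clinical trial".

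**Comparator.** The Abstract (Intervention) and section 2.3 describe a dietitian-led, medically supervised diet following the AGHE. The Discussion says that this diet "is likely superior in terms of its health effects compared to" what participants usually eat. No inert or sham diet appears anywhere.

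**Blinding.** Section 2.1.3 blinds participants to the study hypothesis and keeps clinicians blind to allocation as far as possible. It does not claim that participants are blind to their diet.

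**Question.** The Abstract (Objectives) states the aim as the effects of nutritional ketosis, reached through a modified ketogenic diet. The last paragraph of the Introduction says that a trial in this field should compare KD with another diet under otherwise identical circumstances "to establish the specific contribution of the ketotic metabolic state on the outcomes of interest".

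**Equal treatment.** Section 2.1.3: "Participants in both groups will be treated identically in all respects except for the intervention being tested".

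**What comes with the KD arm.** Section 2.2 sets its macronutrients and says that participants on it are "recommended to supplement with a CHO-free multivitamin". Section 2.1.2 says that metabolic medication might be adjusted for the KD group. The control diet is set out in section 2.3, "with protein comprising 11%, fats ranging from 20 to 35%, and the remainder from carbohydrates".

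**Safeguard.** The limitations paragraph of the Discussion offers correlation of daily ketone levels with the psychiatric and cognitive results as an objective control measure for expectation bias and for unblinding of assessors.

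**The concern.** A placebo label tells a reader two things: that the comparator is inert, and that expectation is balanced because participants cannot tell what they receive. The protocol's own description supports neither. A null result would mean no advantage over another improved diet, which is different from no advantage over placebo. A positive result would be a difference between two diets whose recipients know which one they are eating.

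The second issue is attribution. The stated objective concerns ketosis, while the thing randomised is a diet with its accompanying advice and care. If the ketone-outcome correlation is then accepted as a control for expectation, a reader may take an observational association as proof that ketosis caused the difference.

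**Working it through.** This is mainly a comparison of sections. The arithmetic serves only to size the dietary contrast.

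**1. Is there a placebo?** Every section that describes the comparator (Abstract Intervention, 2.3, Table 3, 8.1) names the AGHE diet. The Introduction itself speaks of another dietary intervention. The label is therefore wrong, although the comparator is openly stated.

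**2. Do participants know their diet?** Under section 2.1.2 they receive group-specific education, prepare their own meals and keep daily food diaries. Under section 7.4 the monitor tells them their time in ketosis. The Discussion accepts that some may disclose their diet to the psychiatrist and that some assigned to KD may hold expectations of benefit.

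**3. Who rates the outcomes?** Of the primary measures, PANSS and YMRS are clinician interviews (3.1, 3.2), so blind assessment is possible for them. The BDI is self-report (3.4) and WHODAS 2.0 is patient-reported (3.3). For these two the rater is the participant, who knows the diet.

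**4. What does randomisation identify?** It identifies the effect of assignment to KD with all that goes with it, against assignment to AGHE with all that goes with it. The KD package contains the macronutrient change, the multivitamin recommendation and possible adjustment of metabolic medication. With two arms there is one contrast, so the ketosis share of it is not estimable.

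**5. Size of the dietary contrast.** Energy intake is assumed to be 2,000 kcal/day in both arms, at 4 kcal/g for protein and carbohydrate; the documents give no common energy figure.

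- KD protein in section 2.2: 100% - 75% - 5% = 20%, which agrees with Table 2. Table 3 gives 10-20%, so 20% is the top of that range.
- KD protein: 0.10 × 2000 / 4 = 50 g to 0.20 × 2000 / 4 = 100 g.
- Control protein: 0.11 × 2000 / 4 = 55 g.
- Difference: 50 - 55 = -5 g to 100 - 55 = +45 g per day.
- Carbohydrate: KD 0.05 × 2000 / 4 = 25 g (section 2.2). Control is 100% - 11% - 35% = 54% to 100% - 11% - 20% = 69%, or 270 to 345 g. This gap is how the diet produces ketosis and is not counted as a separate co-intervention.

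**6. Does the ketone correlation restore the ketosis-specific conclusion?** Ketone level is measured after randomisation and depends on how closely a participant follows the diet. Adherence may go with motivation, expectation and illness severity. Participants also see their own readings, so expectation may itself follow the ketone level. The association is not protected by randomisation and cannot remove the bias that it is offered to control.

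**7. Is the sample size affected?** No. Section 8.1 already plans on KD (75%) against AGHE (40%). With pooled variance, n per arm = [1.960 × √(2 × 0.575 × 0.425) + 1.2816 × √(0.75 × 0.25 + 0.40 × 0.60)]² / 0.35² = (1.370 + 0.838)² / 0.1225 = 39.8, hence 40 per arm and 80 in total; 80 / 0.80 = 100. The stated figures reproduce.

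**The case against.** The strongest reply is that everything beyond the label is already in order. Much of it stands, and it rules out several stronger readings.

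- *A reader might infer that the Introduction claims this trial isolates ketosis.* That sentence says what such a trial ought to do, and its examples of identical circumstances are management, attention and outcome measures. The sentence after it gives this trial's aim as the efficacy of ketogenic metabolic therapy. The ketosis wording that binds this trial is the Abstract's objective.
- *A reader might infer that section 2.1.3 is contradicted by the multivitamin.* It exempts the intervention being tested, and the multivitamin sits under the heading Experimental intervention. Read that way the two agree. The same reading makes the intervention a package.
- *A reader might infer that medication is adjusted in the KD arm alone.* Section 2.1.2 does not say so. It names the KD group for a possible adjustment, but the sentence before it leaves existing treatment to the treating team, without limiting this to one arm.
- *A reader might infer that KD participants get about twice the protein.* That takes the top of the range; at the bottom of Table 3's range the KD figure is slightly below control.
- *A reader might infer that limitations are hidden.* They are not. The Discussion concedes expectation bias, possible unblinding, and that human studies rarely show exact mechanisms directly. It also seeks benefit beyond the control diet, so the diet-against-diet question is visible.

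What this does not answer is the placebo label in two places, the objective worded as ketosis, and the correlation described as a control measure.

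**Conclusion.** The point holds in a limited form. The placebo label is a stated property that the design does not have. The design supports a conclusion about the KD package against the AGHE package, with participants aware of their diet. It does not support a conclusion against placebo or about ketosis alone, and the ketone correlation does not close that gap.

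The size is one of interpretation, with no error in a number. The randomised comparison remains valid and the sample size reproduces. The protein difference, if cited, is about -5 to +45 g/day, and this rests on the assumed 2,000 kcal in both arms. That participants know their diet is inferred from the education, diaries, meal preparation and meter readings that the protocol describes. Nothing here bears on whether the supplement advice or medication handling is clinically right.

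**What to change.** - **Abstract (Design) and section 2.1:** replace the placebo wording with, for example, *active-diet-controlled; participants not blinded to diet; clinician-rated outcomes assessed blind as far as possible; BDI and WHODAS 2.0 participant-reported*. A bare assessor-blinded label would overstate the position for the last two.
- **Abstract (Objectives) and end of the Introduction:** state the question as the KD package against the AGHE package.
- **Discussion, limitations:** call ketone-outcome correlations exploratory, and do not describe them as a control for expectation bias or unblinding.
- **Section 2.1.3:** make clear that the multivitamin advice (2.2) and possible medication adjustment (2.1.2) belong to the KD package, or reconcile those sections with the statement of identical treatment. Either is acceptable statistically, and neither implies which practice is right.
- **If protein is mentioned as an arm difference,** give the range (KD 10-20%, about 20% in section 2.2, against 11%) and not a single gap.

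The cost is a few sentences. No analysis or sample size changes. The downside is a less ambitious mechanistic claim.
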